# Efficacy of an Internet-based intervention with self-applied exposure therapy in virtual reality for people with panic disorder: study protocol for a randomized controlled trial

**DOI:** 10.1186/s13063-023-07536-1

**Published:** 2023-08-12

**Keywords:** Online intervention, CBT, Anxiety, Panic disorder, Internet, Guided self-help, Exposure

## Abstract

**Background:**

Due to several treatment barriers, many individuals with panic disorder do not receive evidence-based treatment. One promising option to narrow this treatment gap is Internet-based psychotherapy, which has been shown particularly effective in guided formats. Still, there remains room for improvement to make these digital therapies more accessible, cost-efficient, and aligned with best practices for in-person interventions (e.g., exposure). The smartphone app “Invirto – Treatment for Anxiety” offers digitally guided, evidence-based treatment of panic disorders including virtual reality (VR) for exposure therapy. The aim present study is to investigate the efficacy, safety, and acceptance of Invirto in comparison to a care-as-usual (CAU) control group.

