	Understanding diversity of emotions
	Understanding emotions as indicators of needs
	Learning to accept emotions
8	Review of the treatment and what has been achieved
	Advice on how to deal with risky situations
	Preparation of an emergency kit
	Tips for further practice
	Planning for the next phase of exercises

The main objective of the planned study is to investigate the efficacy of Invirto in comparison to a care-as-usual (CAU) control group as well as its safety and acceptance over the intervention period of 12 weeks. The primary outcome is the change in the Beck Anxiety Inventory (BAI) from baseline (t0) to post (t1) assessment after 3 months. Secondary outcomes to investigate efficacy include anxiety symptoms (measured by the Panic and Agoraphobia Scale, PAS), quality of life (measured by the Quality of Life–global item, WHOQOL-BREF), depressive symptoms (measured by the Beck Depression Inventory, BDI-II), and psychological flexibility (measured by the Acceptance and Action Questionnaire-II, AAQ-II), as well as body-related anxiety, catastrophizing cognitions, and mobility avoidance (measured by the Questionnaire on panic-related Anxieties, Cognitions and Avoidance, ACA). Acceptance will be measured by the Client Satisfaction Questionnaire (CSQ-8) and the Treatment Adherence Perception Questionnaire (TAPQ-adapt). Safety will be assessed by the Positive and Negative Effects of Psychotherapy Scale for Internet-based Interventions (PANEPS-I) as well as the Peritraumatic Dissociative Experiences Questionnaire (PDEQ-adapt) to assess dissociation during VR exposure. The CAU group will receive Invirto after assessment at t1. We hypothesize that anxiety symptoms will decrease more in the Invirto group from t0 to t1 compared to the CAU group and that Invirto will be a safe and accepted intervention. In addition, we expect the decrease in anxiety symptoms in the intervention group to be sustained from t1 to t2. Furthermore, we expect a decrease in both the primary and secondary outcomes from t1 to t2 in the CAU group.

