##### Positive and Negative Effects of Psychotherapy Scale for Internet-based Interventions (PANEPS-I)

The PANEPS-I [46], an adjusted version of the PANEPS [47] in which the wording of some items has been adapted, will be used in the current study at t1 and t2. The PANEPS-I is a self-report questionnaire assessing positive effects and adverse events during the individual’s most recent used digital intervention. The PANEPS-I is divided into four subscales with a total of 29 items: Positive Effects, Unethical Conduct, Malpractice, and Side Effects. All subscales of the PANEPS have strong internal consistency, with Cronbach’s *α* values ranging from 0.72 to 0.92 [46].

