##### Adapted Peritraumatic Dissociative Experiences Questionnaire (PDEQ-adapt)

The PDEQ by Marmar et al. [48] is a standardized self-report 10-item questionnaire that retrospectively assesses dissociation, depersonalization, and derealization experiences during a traumatic event. Participants are asked to rate statements regarding dissociation on a five-point scale ranging from “(1) not at all true” to “(5) extremely true” at t1 and t2. An overall PDEQ score is calculated by summing the scores, with higher scores indicating more severe symptoms. Internal consistency shows a Cronbach’s *α* of 0.89 [48]. In the present study, we used an adapted version of the PDEQ (PDEQ-adapt) by reformulating the items to ask about dissociation during VR exposure instead of a past traumatic event.

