### Data collection and management

Data collection and management will be carried out by the study center. All data for hypothesis testing will be collected online in clinically validated, standardized questionnaires (self-report) at three assessment points (t0 = baseline; t1 = three months after baseline; t2 = 6 months after baseline). For the online assessment, all participants will be encouraged to create an e-mail account that does not contain any personally identifying information. No additional personal information (such as names or addresses) will be gathered at t0, t1, or t2. Data security is guaranteed during all phases of the study. After confirming their participation with the digital consent form, the study participants will complete the study-related questionnaires to record the endpoints (BAI, PAS, WHOQOL-BREF, AAQ-II, BDI-II, ACA) for baseline assessment (t0). The survey instruments are presented in the “Measure” section. The baseline assessment takes approximately 20 to 30 min. Subsequently, participants will be randomly assigned to one of the two study groups (intervention group vs. CAU) and informed about this allocation. The participants in the intervention group will start the treatment with Invirto. The participants in the control group will receive care as usual (CAU). For post assessment (t1), the study participants will be asked to complete the questionnaires from t0 plus four additional ones (BAI, PAS, ACA, WHOQOL-BREF, AAQ-II, BDI-II, CSQ-8, PANEPS, TAPQ-adapt, PDEQ-adapt, IPQ, PANEPS-I). After that, the control group will be given access to the intervention Invirto. After a further 3 months, that is 6 months after baseline (t2), all participants will complete all the study questionnaires online once again (BAI, PAS, ACA, WHOQOL-BREF, AAQ-II, BDI-II, CSQ-8, PANEPS-I, TAPQ-adapt, PDEQ-adapt, IPQ, PANEPS-I). This is the end of the data collection in the study. For an overview of the assessment of all primary and secondary outcome measures, see Table 2. Trial methodology was planned according to the "Standard Protocol Items: Recommendations for Interventional Trials (SPIRIT)". For more information see Additional file 1. 

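### The abstract's aim to compare safety with CAU is not supported by the named safety measures, which lack a proper referent in CAU at t1 and have no baseline value

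*Protocol article*

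**What the plan says.** The aim in the abstract (Background) is to "investigate the efficacy, safety, and acceptance of Invirto in comparison to a care-as-usual (CAU) control group". The objectives at the end of the Invirto therapy section compare efficacy with CAU and then add "as well as its safety and acceptance over the intervention period of 12 weeks". The hypothesis there is that "Invirto will be a safe and accepted intervention", with no comparator and no criterion.

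The same section names two safety measures:

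- PANEPS-I, described under Measures as "assessing positive effects and adverse events during the individual’s most recent used digital intervention".
- PDEQ-adapt, made by "reformulating the items to ask about dissociation during VR exposure instead of a past traumatic event".

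Table 2 schedules both at t1 and t2 only. Under Study design, CAU participants get access to Invirto after t1. The abstract (Methods) lists both scales among the secondary outcomes, with PANEPS-I grouped under treatment satisfaction, and expects a larger t0-to-t1 change in the intervention group for primary and secondary outcomes. Statistical analyses applies the rationale of the primary analysis, an ANCOVA with the baseline score as covariate, to the secondary parameters.

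Data collection and management gives the t1 battery to study participants without separating the arms: "BAI, PAS, ACA, WHOQOL-BREF, AAQ-II, BDI-II, CSQ-8, PANEPS, TAPQ-adapt, PDEQ-adapt, IPQ, PANEPS-I". Ethical aspects and data safety names adverse event recording and reporting as a principle of the GCP framework, and says that reasons for withdrawal will be asked for and evaluated.

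**The concern.** A comparison of safety with CAU needs a harm measure that means the same thing in both randomised arms while one of them is unexposed. The two named instruments instead ask about the experience of a treatment that the control arm has not yet been given. The analysis assigned to them also needs a baseline value that is never collected.

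What is at stake is the safety conclusion. As described, it could rest on the ratings of treated participants who completed the questionnaires, with no control rate and no criterion. BAI, PAS and BDI-II are collected in both arms at t0 and t1, but the article analyses them only as mean differences. A favourable mean difference can coexist with a minority who deteriorate during self-applied exposure.

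**Working it through.** **1. What each measure can deliver by arm and time**

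| Measure | t0 | t1, Invirto arm | t1, CAU arm | t2 |
|---|---|---|---|---|
| PDEQ-adapt | not collected | VR exposure in Invirto | no trial-provided VR exposure to rate | both arms have had access |
| PANEPS-I | not collected | Invirto, or any later digital product | only some other digital intervention | both arms have had access |
| BAI, PAS, BDI-II | collected | collected | collected | collected |

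At t2 a between-arm contrast compares earlier with later access, not exposed with unexposed. With no t0 value, neither a t0-to-t1 change nor a baseline covariate exists for PDEQ-adapt or PANEPS-I.

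**2. The plan's own figure**

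The article gives no figure for safety. Its sample size reproduces: an ANCOVA with two groups and one covariate, f = 0.28, two-sided α = 0.05 and noncentrality f²·N gives N = 103 (power 0.804). Allowing for 20% dropout, 103/0.80 = 128.75, so 129 against the stated 128, a difference of no consequence. This figure covers the primary analysis only. At 1:1 it gives 128/2 = 64 per arm, and 64 × 0.80 ≈ 51 after dropout.

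**3. Worsening thresholds from the stated reliabilities**

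The threshold in baseline SD units is 1.96·√(2(1 − α)), taking the quoted Cronbach's α as the reliability:

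- BAI, α = 0.90: 1.96·√0.20 = 0.88 SD
- PAS, α = 0.86: 1.96·√0.28 = 1.04 SD
- BDI-II, α = 0.89: 1.96·√0.22 = 0.92 SD

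**4. Precision of a between-arm worsening rate**

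The documents give no worsening rate, so the rates below are assumptions. The half-width of the 95% CI is 1.96·√[p₁(1 − p₁)/n + p₂(1 − p₂)/n].

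- 5% vs 10%, n = 64: 1.96·√[(0.0475 + 0.0900)/64] = 0.091
- 5% vs 10%, n = 51: 1.96·√[(0.0475 + 0.0900)/51] = 0.102
- 5% in both arms: ±7.6 points at 64 and ±8.5 at 51
- 10% in both arms: ±10.4 points at 64 and ±11.6 at 51

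Power for a test at two-sided 0.05:

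| Assumed rates | 64 per arm | 51 per arm |
|---|---|---|
| 5% vs 10% | 0.19 | 0.16 |
| 5% vs 15% | 0.47 | 0.39 |
| 10% vs 20% | 0.35 | 0.29 |

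At 64 per arm, 80% power is reached only for a rise from 5% to about 22%, or from 10% to about 30%. If nobody in an arm worsens, the one-sided 95% upper bound 1 − 0.05^(1/n) is 4.6% at 64 and 5.7% at 51. These figures support an estimate with an interval, not a test.

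**5. Counting dropouts as worsened**

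Assume 20% dropout in each arm and 5% vs 10% among completers. The rates become 0.8 × 5% + 20% = 24% and 0.8 × 10% + 20% = 28%. The difference is 4 points, with half-width 1.96·√[(0.24·0.76 + 0.28·0.72)/64] = 0.152. Equal dropout dilutes the contrast, so this analysis mainly shows how far unequal dropout could move the result.

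**The case against.** The strongest reply is that only the abstract makes safety comparative. The main text attaches the comparison to efficacy, and its safety hypothesis has no comparator. On that reading, user-only instruments fit the aim, and rewording the abstract cures the mismatch. This stands as a description of the main text, and it is why dropping the comparison is an acceptable remedy. It does not rescue the abstract's aim, and it leaves the t0-to-t1 expectation and the baseline-adjusted ANCOVA inapplicable to both scales.

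A reader might go further and infer three things that the documents do not support.

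- **That only Invirto or VR users can answer either scale.** This fits PDEQ-adapt. PANEPS-I refers to the "most recent used digital intervention", so a CAU participant who used another programme could answer it, although the answer would say nothing about Invirto. The t1 battery also lists PANEPS beside PANEPS-I. That may be a slip in the list, and the article does not explain it.
- **That the trial has no comparative safety data at all, and no view of people who leave.** Adverse event recording is named, and could be compared if done alike in both arms. How this is done may sit in the full protocol. Reasons for withdrawal are to be evaluated.
- **That worsening rates would settle safety.** They say nothing about dissociation in VR, side effects or malpractice, and their intervals are wide.

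It is also fair to say that a deterioration analysis could be left to a statistical analysis plan. Its absence alone would not be a finding. The finding is that the article states an aim and an analysis that its named measures cannot deliver.

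**Conclusion.** The point holds in this limited form: the abstract's comparison of safety with CAU is not supported by the named safety measures, and the stated analysis cannot be run on them because neither has a baseline. That part follows from the text and needs no assumption. It should be corrected, but it does not touch the primary BAI analysis.

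A comparative estimate of symptom worsening is available from data already collected, with modest precision: about ±9 percentage points at 64 per arm and ±10 at 51. Those widths rest on assumed rates of 5% and 10%. The thresholds rest on the quoted α values standing in for reliability in this sample. Any safety statement from a trial of this size must be correspondingly modest.

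**What to change.** 1. State that PANEPS-I and PDEQ-adapt are descriptive in exposed participants only, and exempt them from the t0-to-t1 expectation and the baseline-adjusted ANCOVA. Correct or explain the PANEPS entry in the t1 battery.
2. Prespecify, as a comparative estimate of symptom worsening and not of safety as a whole, the proportion per arm worsening from t0 to t1 beyond the scale-specific threshold on BAI, PAS and BDI-II. Report the risk difference with 95% CI and no test, in all randomised participants.
3. Use the planned multiple imputation, classifying worsening from the imputed scores. Standard imputation assumes data missing at random and so does not address people who leave because they got worse. Add the sensitivity analysis that counts dropouts as worsened.
4. State whether adverse events are recorded in the same way in both arms.
5. If the sponsor does not want items 2 and 3, remove the comparison with CAU for safety from the abstract, so that it agrees with the main text.

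The cost is small: a short amendment and one added analysis, with no new data collection for items 1 to 3. Trial status says that no data had been extracted or analysed at submission and that changes go into an amendment, so the change could still be prespecified at that point. The downside is wide intervals and a more cautious safety claim.

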**Methods:**

We plan to conduct a randomized controlled trial with two conditions (intervention vs. CAU), three assessment times via online surveys (t0: baseline; t1: 3 months after baseline; t2: follow-up assessment 6 months after baseline), and a total of 128 participants with a clinical diagnosis of panic disorder (symptoms must be experienced ≥ 1 year). Recruitment will take place via email, phone, and the study website. The primary outcome will be the change in anxiety symptoms as measured by Beck’s Anxiety Inventory from t0 to t1. Secondary outcomes will be the change in anxiety symptoms (measured by the Panic and Agoraphobia Scale, PAS; Questionnaire on panic-related Anxieties, Cognitions and Avoidance, ACA), depressive symptoms (measured by the Beck-Depression-Inventory, BDI-II), treatment satisfaction (measured by the Client Satisfaction Questionnaire, CSQ-8; Treatment Adherence Perception Questionnaire, TAPQ-adapt; Positive and Negative Effects of Psychotherapy Scale, PANEPS-I), psychological flexibility (measured by the Acceptance and Action Questionnaire-II, AAQ-II), and dissociation during VR exposure (measured by an adapted version of the Peritraumatic Dissociative Experiences Questionnaire, PDEQ-adapt). Participants in the intervention group will receive access to the intervention (Invirto) right after t0, while the CAU group will receive access to Invirto after t1. We expect a larger change in both the primary and secondary outcomes from t0 to t1 in the intervention group in comparison to the CAU group.

**Discussion:**

This study is one of the first to evaluate an Internet-based intervention for people with panic disorder that includes self-application of VR exposure therapy. The findings are expected to extend the body of knowledge about effective Internet-based treatment options for people with panic disorder. The empirical and clinical implications and the limitations of the study are discussed.

**Trial registration:**

DRKS00027585 (www.drks.de/drks_web/), date of registration: 13 January 2022.

**Supplementary Information:**

The online version contains supplementary material available at 10.1186/s13063-023-07536-1.

## Background

### Panic disorder and treatment strategies

People with panic disorder suffer from recurrent and unpredictable anxiety attacks that are accompanied by severe physical symptoms such as feelings of suffocation, rapid heartbeat, or chest pain. They often make significant changes in their behavior to avoid future anxiety attacks and experience severe limitations in their daily life activities [1]. The 12-month prevalence for panic disorder is 2–3% in the general population [2, 3]. Panic disorder is associated with high indirect and direct health care costs due to patients’ assumption that a physical illness is causing their alarming symptoms [4], resulting in frequent, inconclusive, and costly physical examinations and emergency medical admissions. Due to the direct and indirect costs to the health care system, anxiety disorders (all ICD-10 F4x- diagnoses) generated the fourth highest aggregate costs across the EU—74 billion Euros in 2010 [5].

According to German [6] and international guidelines such as the National Institute for Clinical Excellence (NICE; [7]), cognitive behavioral therapy (CBT) that includes exposure therapy is the first-line approach in the treatment of panic disorders (with or without agoraphobia). With and/or without the support of a therapist, the patients expose themselves to anxiety-provoking situations and gain new insights into their alarming physical symptoms and their need for safety strategies and avoidance [8]. Whereas Foa and Kozak [9] emphasize the mechanism of habituation in their “emotional processing theory,” Craske [10] highlights the importance of the approach of inhibitory learning and inhibitory regulation to maximize the effectiveness of exposure therapy.

### Internet-based psychotherapy

Although psychotherapy has been proved effective with large effect sizes compared to no treatment [11], many people with panic disorder never receive psychological treatment [12]. Reasons for this treatment gap may include barriers to treatment, which include a shortage of trained therapists, high treatment costs, and the shame and stigma around seeking psychological help [13]. One option to address these barriers is to offer psychotherapy in the form of Internet-based cognitive behavioral therapy (iCBT). Internet-based therapy enables treatment flexibility independent of time and place and also provides a cost-effective way to counteract treatment barriers [14]. iCBT offers low-threshold access to evidence-based and guideline-compliant treatment for various mental disorders. Most commonly, iCBT includes structured guided (accompanied by a therapist) or unguided (self-help interventions) digital treatment programs. In the case of structured interventions, the content is presented either on an Internet platform or through a smartphone app.

In recent years, numerous studies have evaluated Internet-based therapies for various mental disorders, including depression [15], obsessive–compulsive disorder [16], and anxiety disorders [17]. In reviewing the effectiveness of iCBT, cross-disorder studies have demonstrated a positive impact of Internet-based treatment programs with a medium effect size [18]. The amount of therapeutic contact influences the effectiveness of iCBT; unguided self-help interventions (no contact between patient and therapist except for baseline assessment) showed the smallest effect size compared to minimally guided interventions (minimal contact beyond the assessment to assist with use of the self-help intervention) and mostly guided interventions (regular contact between the patient and therapist; [19]).

Regarding anxiety disorders, meta-analytic research shows that psychological interventions delivered via smartphone devices can significantly reduce anxiety symptomatology with moderate to large effect sizes [20]. Firth et al. [21] found significantly greater reduction in anxiety symptoms with smartphone interventions than control conditions (*g* = 0.33). However, effect sizes from smartphone interventions were significantly larger when compared to waitlist/inactive controls (*g* = 0.45) than to active control conditions (*g* = 0.19).

Meta-analyses of guided iCBT programs for panic disorder have found large mean between-group effects on panic severity when compared to waitlist or control conditions [22–24]. In a meta-analysis in which iCBT was directly compared to face-to-face CBT, Carlbring et al. [25] found equivalent efficacy between the two modalities regarding panic symptoms, indicating that the two treatment formats are equally effective.

Exposure and interoceptive exposure are two of the most effective components of face-to-face CBT [26, 27]. Exposure treatment can be effectively represented digitally. Kim et al. [28] investigated the efficacy of a self-training in virtual reality (VR) for patients with social anxiety disorder (SAD) and showed that the VR program provided significant improvements in anxiety symptoms and positive changes in social components such as total speech length, subjective nervousness, and subjective confidence.

### Invirto therapy

The smartphone app “Invirto – Treatment for Anxiety” (“Invirto” for short; developed by Sympatient Ltd.) allows digitally guided, evidence-based treatment of panic disorders. It aims to enable patients to tackle their anxiety symptomology themselves, reduce functional limitations caused by the panic disorder, and improve their quality of life. Invirto includes more than 12 h of digital therapeutic content divided into 8 modules with audio and video content. See Table 1 for more information about the content of each module of Invirto. One component of the treatment is digital exposure therapy in VR. Invirto offers virtual reality exercises that mirror the situations that people with panic disorder find challenging and often avoid. These include simulated situations such as taking a subway or bus ride, standing in a long checkout line at the supermarket, being underground in a tunnel, or using an elevator. It also includes interoceptive exposure exercises to re-evaluate the individual’s physical symptoms of anxiety. Each VR exposure exercise is guided by an audio-recorded therapist and can be performed for up to 90 min. Although several iCBT applications for anxiety disorders have been developed in recent years, to date Invirto is the only digital therapy app that uses VR.

**Table 1 Tab1:** Modules and content of Invirto

Module #	Content and aim of module
1	Provide overview of treatment, explain psychotherapy
	Explain use of the app
	Emulate a therapeutic relationship
	Explain panic disorder, reducing stigma
	Manage expectations
2	Visualize limitations in everyday life due to anxiety (create cognitive dissonance about the status quo)
	Define problems, symptoms, and fears
	Validate the difficulty of change
	Discuss costs and benefits of changing behavior
	Define goals for the intervention
3	Healthy and pathological anxiety
	Self-reinforcing feedback loops
	Identification of conditions of developing and maintaining factors of anxiety
	Self-observation of anxiety situations and occurrence of anxiety
4	Problems due to avoidance/safety behavior
	Breathing technique for panic attacks, relaxation techniques
	Autonomic nervous system
	Sympathetic and parasympathetic nervous systems
5	Typical thoughts in anxiety
	Effects of anxiety thoughts
	Exploration of one’s own anxiety thoughts
6	Rationale for exposure
	Exercise in virtual reality
7	Understanding the function of emotions
	Understanding the relationship between emotion avoidance and fear
	Understanding diversity of emotions
	Understanding emotions as indicators of needs
	Learning to accept emotions
8	Review of the treatment and what has been achieved
	Advice on how to deal with risky situations
	Preparation of an emergency kit
	Tips for further practice
	Planning for the next phase of exercises

The main objective of the planned study is to investigate the efficacy of Invirto in comparison to a care-as-usual (CAU) control group as well as its safety and acceptance over the intervention period of 12 weeks. The primary outcome is the change in the Beck Anxiety Inventory (BAI) from baseline (t0) to post (t1) assessment after 3 months. Secondary outcomes to investigate efficacy include anxiety symptoms (measured by the Panic and Agoraphobia Scale, PAS), quality of life (measured by the Quality of Life–global item, WHOQOL-BREF), depressive symptoms (measured by the Beck Depression Inventory, BDI-II), and psychological flexibility (measured by the Acceptance and Action Questionnaire-II, AAQ-II), as well as body-related anxiety, catastrophizing cognitions, and mobility avoidance (measured by the Questionnaire on panic-related Anxieties, Cognitions and Avoidance, ACA). Acceptance will be measured by the Client Satisfaction Questionnaire (CSQ-8) and the Treatment Adherence Perception Questionnaire (TAPQ-adapt). Safety will be assessed by the Positive and Negative Effects of Psychotherapy Scale for Internet-based Interventions (PANEPS-I) as well as the Peritraumatic Dissociative Experiences Questionnaire (PDEQ-adapt) to assess dissociation during VR exposure. The CAU group will receive Invirto after assessment at t1. We hypothesize that anxiety symptoms will decrease more in the Invirto group from t0 to t1 compared to the CAU group and that Invirto will be a safe and accepted intervention. In addition, we expect the decrease in anxiety symptoms in the intervention group to be sustained from t1 to t2. Furthermore, we expect a decrease in both the primary and secondary outcomes from t1 to t2 in the CAU group.

